**4.2 Study Population****4.2.1 Subject disposition**

Descriptive statistics will be performed for subjects screened, randomized, treated, dropped out and reasons for dropout by treatment groups, and the number and percentage of subjects in each category will be calculated. If necessary, summary statistics by site will be provided.

Descriptive statistics will be performed on the subjects' enrollment in each analysis dataset and reasons for exclusion, and the number of cases and percentage will be calculated.

Screening, randomization, and treatment of subjects in the trial were tabulated.

**4.2.2 Protocol Violation/Deviation**

The number and percentage of protocol violations/deviations will be summarized by category for each treatment groups. Major protocol violations/deviations will be listed by subject.

**4.2.3 Demographic Characteristics and Disease Baseline Conditions**

Demographic characteristics and disease baseline conditions will be summarized by treatment groups on the FAS. Number of non-missing values, mean, standard deviation, median, minimum,

and maximum were calculated for continuous variables. Discrete variables were calculated as frequency and percentage.

Demographic characteristics included age, sex, height, weight, body mass index. Vital signs including supine systolic blood pressure, and diastolic blood pressure, will also be listed and summarized in each treatment group. Baseline disease conditions included mRS score, NIHSS score, stroke history, stroke classification, and renal function.

#### **4.2.4 Medical History**

Medical history will be statistically analyzed by treatment groups based on FAS set.

Medical history was coded using the applicable version of MedDRA at the time of data analysis and summarized by system organ class and preferred term by treatment groups.

Medical history will be detailed in listings.

### **4.3 Efficacy analysis**

#### **4.3.1 Primary Efficacy Endpoint and Analyses**

The primary efficacy measure in this trial was the proportion of subjects with mRS score  $\leq 1$  at Day 90 of treatment. The main estimated target attributes under the estimated target framework are presented in Section 2.4, and the different coping strategies proposed for the intercurrent events are as follows:

- **Treatment Policy Strategy**

When subjects participating in the trial were successfully randomized and treated, if concomitant medication/therapy was used during the treatment period (see Section 5.8 of the protocol), the investigator did not terminate the treatment or allow them to withdraw prematurely from the study according to the actual situation; or the subject did not withdraw prematurely from the study despite dose delay, interruption, or termination due to an AE; or because of a new coronavirus outbreak, the subject mRS score could only be obtained remotely. For such intercurrent events, the primary efficacy measure will be handled by the treatment policy strategy, i.e., the mRS achievement or failure will be discriminated according to the collected measured mRS score (remote visit mRS score will be considered valid) regardless of whether the intercurrent event occurred.

- **Composite Variable Strategy**

When a randomized subject had no mRS score after starting treatment for any reason; or the subject prematurely withdrew from protocol-specified follow-up because of an AE. Such intercurrent events will be handled for the primary efficacy measure using a composite variable strategy, i.e., the occurrence of such events will be considered as having a mRS score  $> 1$  at the end of follow-up (Day 90 post-treatment).

- **While-on-Treatment Strategy**

When subjects participating in the trial prematurely discontinue treatment or withdraw from the study for reasons other than those mentioned in the above strategy, the on-treatment strategy will be used to deal with the primary efficacy indicators, that is, the mRS score closest to the time of withdrawal will be used as the basis for judging whether the mRS is up to standard.

Missing values for the primary efficacy measure will be handled accordingly by different handling strategies for the above intercurrent events, and subjects who prematurely discontinue treatment or withdraw from follow-up due to emergency unblinding resulting in missing mRS scores on Day 90 will be handled as one of the coping strategies for the above intercurrent events for reasons documented in the CRF.

Primary efficacy endpoint analysis will be performed on FAS and PPS separately.

Primary Estimated Method:

Descriptive statistics were performed on the proportion of subjects with mRS score  $\leq 1$  at Day 90 by treatment groups, the number and percentage of subjects with mRS score  $\leq 1$  at Day 90 of treatment were calculated, and the rate difference between the two groups (investigational group - control group) and 95% confidence interval were calculated based on the normal-approximation. Odds ratios (ORs) with 95% CIs were calculated using logistic regression.

Considering that the interim analysis (done by IDMC and independent statistical team) will be performed in this study after 50% of subjects have completed the 90-day visit, and an unblinded sample size re-estimation will be performed, and in case of sample size adjustment, p values will be calculated based on the statistics obtained after correction by the CHW method, and ORs and 95% confidence intervals will be further estimated. If the lower limit of the 95% confidence interval of the OR was  $> 1$ , the investigational group was considered to have better efficacy than the control group. The main analysis of the primary efficacy indicators is mainly based on the FAS results, and the inconsistent FAS results and PPS results need to be further explored.

---

- Sensitivity Analysis

Sensitivity analyses were performed on the FAS only.

Sensitivity Analysis 1:

Missing data on the primary efficacy outcome was imputed with best case analysis (assume any subject missing 90-day outcome to be mRS score  $\leq 1$ ). Logistic regression analysis was performed to calculate the OR and 95% confidence interval.

Sensitivity Analysis 2:

Missing data on the primary efficacy outcome was imputed with Worst case analysis (assume any subject missing 90-day outcome to be mRS score  $> 1$ ). Logistic regression analysis was performed to calculate the OR and 95% confidence interval.

Sensitivity Analysis 3:

Missing data on the primary efficacy outcome was imputed with LOCF combined with best case analysis (assume any subject missing 90-day outcome after LOCF to be mRS score  $\leq 1$ ). Logistic regression analysis was performed to calculate the OR and 95% confidence interval.

Sensitivity Analysis 4:

Missing data on the primary efficacy outcome was imputed with LOCF combined with worst case analysis (assume any subject missing 90-day outcome after LOCF to be mRS score  $> 1$ ). Logistic regression analysis was performed to calculate the OR and 95% confidence interval.

Sensitivity Analysis 5:

Logistic regression analysis was performed to calculate the OR and 95% confidence interval between the investigational and control groups using treatment as the analysis variable and baseline time from actual treatment to onset ( $\leq 24$  hours,  $> 24$  hours), and study site as covariates.

- Subgroup analysis

The primary efficacy endpoint will be analyzed in subgroups according to the following factors:

- Age ( $\leq 65$ ,  $> 65$ )
- Gender (male, female)
- Actual treatment to Onset Category 1 ( $\leq 24$  hours,  $> 24$  hours)

- 
- Premorbid mRS score (0, 1)
  - Pre-treatment NIHSS total score classification ( $\leq 7$ ,  $> 7$ )
  - History of stroke (Yes, No)
  - History of hypertension (Yes, No)
  - History of hyperlipidemia (Yes, No)
  - History of diabetes (Yes, No)
  - History of heart disease (yes, no)
  - Stroke etiology classification
  - Renal function class (normal, mild impairment and moderate to severe impairment as assessed by baseline eGFR)

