### **8.4. Efficacy analysis**

All the analyses were performed in the intention-to-treat population. Missing data on the primary outcome was imputed with treatment policy strategy, composite variable strategies, and while on treatment strategies accounting for intercurrent events, as follows:

- Treatment policy strategy

For the following concomitant events: After the subject is successfully randomized and starts to receive the treatment, concomitant medication/treatment is used during treatment (see Section 5.8) and the investigator does not discontinue the treatment or let the subject withdraw from the study early based on the actual situation; or the subject does not withdraw from the study early despite treatment delay, interruption or discontinuation due to AEs; the subject's mRS score can only be obtained remotely due to the pandemic, The primary efficacy outcomes will be treated by the treatment policy strategy, that is, regardless of whether the concomitant events occur. Whether the mRS reaches the standard will be assessed according to the measured mRS score collected (the mRS score of remote visit is considered valid).

- Composite strategy

For the following concomitant events: Randomized subjects, for whatever reason, do not have an mRS score after the start of the treatment;; or the main reason for the subject's early withdrawal from follow-up prescribed by the protocol is AE, the primary efficacy indexes will be treated by the composite strategy, i.e., the occurrence of such events is considered as

having a mRS score of 6 at the end of follow-up (Day 90 after treatment).

- While on treatment strategy

When a subject discontinues the treatment or withdraws from the study early for reasons other than those mentioned in the composite index strategy, the primary efficacy indexes will be treated by the while on treatment strategy, that is, using the most recent mRS score before the withdrawal from the study as the basis for determining whether the mRS meets the target.

Group difference in the primary efficacy outcome was examined using chi-square test or Fisher exact test, and the corresponding 95% confidence intervals (CIs) of the difference between proportions were estimated based on the normal-approximation. Odds ratios (ORs) with 95% CIs were calculated using logistic regression.

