## 2.5 Sample Size Determination

The sample size for this study was based on the primary efficacy measure, the proportion of subjects with mRS score  $\leq 1$  at Day 90 of treatment. According to previous clinical studies (see Protocol Reference 7-12), it is estimated that the proportion of subjects with mRS score  $\leq 1$  on Day 90 of treatment will be 50% in the investigational group and 40% in the control group, taking a two-sided  $\alpha$  of 0.05, a power of 80%, and a randomization ratio of 1:1. After calculation, 388 subjects are required in each group. Considering a 15% dropout rate, 457 subjects are planned to be randomized in each group, with a total sample size of 914.

An interim analysis is scheduled to be performed after approximately 50% of patients complete the visit on Day 90. The purpose of interim analysis is to re-estimate the sample size based on primary efficacy indexes. It is conducted by the Independent Data Monitoring Committee (IDMC) and whether the sample size should be increased or remain unchanged is recommended according to the regulations of the IDMC. The sample size may be increased to 1.5 times the scheduled sample size at most, and won't be reduced. If the sample size is adjusted, the method proposed by Cui et al. 1999 (hereinafter referred to as the CHW method) will be used to control type I errors in the final analysis.

Interim analyses and sample size re-estimation were performed by an Independent Data Monitoring Committee (IDMC) as detailed in Section 4.5 of this plan and in the IDMC charter.

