## 2.6 Randomization and Blinding

All eligible subjects will be randomly assigned to the investigational or control group according to the ratio of 1:1. The random number table is generated by the standardized software. The detailed parameter settings are set by the randomization plan.

In this trial, a centralized competitive enrollment randomization method will be used, and subjects will be assigned a "screening number" after signing the informed consent form and before performing study-related tests. Subject screening numbers must not be reused.

After the subjects passed screening, the investigator or designee obtained the information of randomization number and corresponding drug number through the randomization system, and distributed the corresponding study drugs according to the randomization number and drug number.

Randomization will be stratified by:

- Onset time:  $\leq 24$  hours vs  $> 24$  hours;
- Investigational site.

The color, description, and packaging (including batch number and shelf life) of the investigational drug (Y-2 sublingual tablet) and placebo control drug (Y-2 sublingual tablet placebo) were identical. Blinding process was completed by statisticians unrelated to this clinical trial. After blinding, the blinding codes will be sealed in duplicate and stored in the leading site and the sponsor, respectively.

The trial was unblinded just once. After the last subject completes the 90-day follow-up in the whole trial, after blind verification, the data is locked and unblinding is performed, that is, the corresponding group of each subject is identified. For interim analysis, according to IDMC charter, unblinded data will be reviewed centrally by IDMC members and their statistical analysis will be performed by a third party unblinded statistician independent of the study project team to ensure blinding during the conduct of the trial.

When a serious adverse event suspected to be related to the investigational drug occurs during the trial, the principal investigator at the site should report to the sponsor to decide whether to initiate the emergency unblinding procedure. Once the blind was broken emergently, the case was treated as a dropout and medication was stopped if the blind was broken emergently during treatment.

This double-blind trial was invalidated if the total blind codes were leaked or emergency unblinding exceeded 20% during the study.

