#### 4.3.2 Secondary Efficacy Endpoints

Secondary efficacy endpoints were analyzed on the FAS and PPS without imputation of missing values.

- mRS score on Day 90 of treatment

Descriptive statistics were performed by treatment groups on mRS scores at Day 90 of treatment to calculate the number of non-missing subjects, mean, standard deviation, median, minimum, and maximum, and at the same time, the number and percentage of subjects with different mRS scores (including missing values) at Day 90 of treatment were calculated. an ordinal logistic regression analysis was performed, with the results presented as common OR and 95% CI, where a common OR in favor of Y-2 sublingual tablet was  $>1.0$

- Proportion of subjects with mRS score  $\leq 2$  at Day 90 of treatment

Descriptive statistics were performed on the number and percentage of subjects with mRS score  $\leq 2$  at Day 90 of treatment as previously described by treatment groups. Comparisons were made between treatment groups using the same logistic regression model as for the primary analysis.

- NIHSS score change from baseline at Day 14 of treatment

Observed values and changes from baseline in NIHSS score at each visit will be summarized descriptively by treatment groups and the number of non-missing subjects, mean, standard

deviation, median, minimum, and maximum will be calculated. Difference in NIHSS score from baseline to Day 14 was be calculated the means with 95% CIs were calculated for each group, and the mean differences with 95% CI between the groups were estimated by generalized linear regression.

- The proportion of NIHSS score of 0-1 at 14, 30, and 90 days of treatment;

The number and percentage of subjects with NIHSS scores of 0 to 1 at 14, 30, and 90 days of treatment will be calculated by treatment groups. Comparisons were made between treatment groups using the same logistic regression model as for the primary analysis.

- Other Efficacy Measures

Not applicable.

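### The primary comparison is unadjusted although randomisation is stratified and baseline NIHSS and age are collected, which gives up some power; protocol, SAP and estimand also do not name the same test

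*Combined protocol and SAP*

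**What the plan says.** SAP 2.6 ("Randomization will be stratified by") lists two factors, onset time (up to 24 hours, or later) and investigational site. Protocol 5.3 lists the same two.

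For the primary endpoint, SAP 4.3.1 gives group proportions, a normal-approximation interval for the rate difference, and then: "Odds ratios (ORs) with 95% CIs were calculated using logistic regression". No covariate is named. Its one success statement is that the lower 95% bound of the odds ratio exceeds 1.

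Onset and site adjust the effect only in Sensitivity Analysis 5, "using treatment as the analysis variable and baseline time from actual treatment to onset", together with site. SAP 4.1.3 computes that time from the first dose, so it is not the stratum used at randomisation.

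Age and baseline NIHSS are described in SAP 4.2.3 and are subgroup factors in SAP 4.3.1. Protocol 8.4 analyses subgroups through treatment-by-subgroup interactions in a logistic model.

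The binary secondaries reuse the primary logistic model (SAP 4.3.2). For the Day 14 NIHSS change, "the mean differences with 95% CI between the groups were estimated by generalized linear regression", with no baseline term stated, although ANCOVA is in the SAP abbreviation list.

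Three places bear on the primary inference:
- Protocol 8.4: "Group difference in the primary efficacy outcome was examined using chi-square test or Fisher exact test", with no rule for choosing between them.
- SAP 4.3.1: the odds-ratio bound.
- SAP 2.4, Table 2-1 (and protocol 2.3): the population summary is the rate difference.

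SAP 2.7, reserved for changes to the protocol's analysis, records none.

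**The concern.** Stratified randomisation removes part of the chance variation between arms. An analysis that ignores the strata still counts that variation in its standard error, so the test is conservative to the extent that the strata predict outcome. Omitting baseline severity and age leaves their chance imbalance in the estimate. Both variables are already in the database and can plausibly predict mRS 0 to 1 at Day 90, so the precision is available at almost no cost. The binary secondaries inherit the same omission.

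The second matter is one of specification. A reader who takes the primary test from the protocol, the SAP or the estimand gets a different statistic from each, and nothing records the move from one to another.

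**Working it through.** **Inputs from the documents.** Rates "50% in the investigational group and 40% in the control group", two-sided 0.05, 80% power, 1:1, 388 per arm, 15% dropout, 457 per arm and 914 in total (SAP 2.5). The FAS is all randomised subjects (SAP 3). There are about 40 centres (protocol abstract), 39 in the second IDMC minutes.

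**Inputs not in the documents, assumed and varied.** The share of outcome variance explained by covariates (R²), the NIHSS distribution, the age, onset and site effects, and the block size.

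**1. Reproduce the plan's figure.** With the pooled-variance formula,

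n = [1.960·√(2·0.45·0.55) + 0.842·√(0.50·0.50 + 0.40·0.60)]² / 0.10² = (1.379 + 0.589)² / 0.01 = 387.3, so 388.

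388 / 0.85 = 456.5, so 457 per arm and 914 in total. All three figures agree with the plan, and the calculation is for an unadjusted two-proportion comparison.

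**2. Unadjusted power with all 457 per arm analysed.** Φ[(0.10·√457 − 1.379) / 0.70] = Φ(1.084) = 86.1%. At 388 per arm it is 80.1%.

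**3. Power with adjustment.** Replace n by n / (1 − R²):

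| Assumed R² | Power, 388 per arm | Power, 457 per arm | Gain at 457 (points) |
|---|---|---|---|
| 0 | 80.1% | 86.1% | – |
| 0.02 | 80.9% | 86.8% | 0.7 |
| 0.05 | 82.0% | 87.8% | 1.7 |
| 0.10 | 84.0% | 89.4% | 3.3 |
| 0.20 | 88.0% | 92.6% | 6.5 |
| 0.30 | 91.8% | 95.4% | 9.3 |

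Simulated logistic regression (4,000 runs per setting, 457 per arm) agrees: 86.5% unadjusted against 89.8% adjusted at R² 0.11, and 85.1% against 91.1% at R² 0.17.

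**4. Simulation of this design, adjusting for onset, NIHSS and age.** Set-up: 914 patients, 39 sites, blocks within site by onset, marginal 50% v 40%. Assumed: skewed NIHSS with median 8, age log-OR −0.02 to −0.03 per year, site SD 0.3 to 0.4. For log-ORs of −0.10, −0.15, −0.20 and −0.25 per NIHSS point:
- 1,200 trials each: gains of 0.6, 2.2, 3.3 and 5.3 points.
- 4,000 trials each: gains of 1.2, 1.4, 3.1 and 4.4 points.

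In the smaller run the squared ratio of mean Z is 1.028 to 1.148, worth 0.028·914 ≈ 26 to 0.148·914 ≈ 135 extra patients.

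**5. Ignoring the strata.** Blocks of 4 in 40 sites by 2 onset strata, 1,500 trials per setting, comparing the unadjusted test with a model holding onset and site dummies:

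| R² of onset and site | Type I error, unadjusted | Type I error, site dummies | Power, unadjusted | Power, site dummies |
|---|---|---|---|---|
| 0 | 5.1% | 5.3% | 87.3% | 87.5% |
| 0.026 | 3.9% | 4.5% | 87.3% | 88.8% |
| 0.066 | 3.7% | 5.3% | 85.5% | 88.0% |
| 0.13 | 4.1% | 5.9% | 87.5% | 90.8% |

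The three prognostic settings average 3.9% for the unadjusted test. The Monte Carlo standard error over 4,500 trials is √(0.05·0.95/4500) = 0.32 points, so the conservatism is real. The 5.9% has a standard error of about 0.56 points (√(0.05·0.95/1500)), so it is a reason for caution about site dummies, not proof of inflation. Sites hold 914/39 ≈ 23 patients, or about 12 per site-by-onset cell if the two onset strata are equal.

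**6. Does the choice of test matter?** Exact enumeration at 457 per arm:
- At 50% v 40%, chi-square, Wald odds ratio and Wald rate difference each have 86.05% power. Fisher has 84.5% and disagrees with them in 1.5% of trials.
- At 40% in both arms, type I error is 4.99% (chi-square), 4.95% (odds ratio), 5.08% (rate difference) and 4.27% (Fisher). Claiming success if any of the four is significant gives 5.08%.

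**The case against.** The best defence is that the plan does what it set out to do. The sample size was built for an unadjusted comparison, which delivers the planned power. Ignoring strata errs on the conservative side, so validity is not threatened. The unadjusted rate difference also targets the estimand's summary directly, whereas an adjusted odds ratio is a different quantity: a marginal 1.50 becomes about 1.58 at R² 0.11 and 1.63 at R² 0.17. All of this stands. It limits the point to efficiency and is why a standardised risk difference belongs beside the adjusted odds ratio.

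It is also fair to object that the size of the gain rests on assumptions. It does: the documents give no prognostic strengths, and at the weak end the gain is under 1 point.

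The most serious practical objection is timing. SAP 4.5.1 takes the interim Z from the same logistic model as the primary analysis, and SAP 4.5 dates the IDMC meeting to 29 April 2022. A new primary model follows an unblinded look. That does not rule out the change, since the decision was not to increase the sample size and the CHW weighting is therefore inactive, but it must be disclosed.

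Two smaller objections are partly right. Protocol 5.5 asks for the first dose as soon as possible after randomisation, so treatment time and randomised stratum should seldom fall in different categories. For the Day 14 NIHSS change, SAP 4.3.2 is silent on covariates, and silence does not prove that baseline is left out. Both still need a sentence in the SAP.

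**Conclusion.** The point holds as a recommended improvement, not as a defect that invalidates the analysis. The primary model is unadjusted by implication, since only Sensitivity Analysis 5 adds covariates. The power forgone at 457 per arm is roughly 1 to 5 points under the prognostic strengths simulated in step 4, and about 9 at R² 0.30. All of these strengths are assumptions.

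Three stronger readings are tempting, and the documents do not support them:
- **That the trial is underpowered.** 388, 457 and 914 all reproduce, and the unadjusted test meets the planned 80%.
- **That NIHSS and age enter no model.** They enter the subgroup interaction models. What is missing is their use to adjust the overall effect.
- **That several success tests compete.** The SAP has one success rule. The fault is that protocol, SAP and estimand do not name the same test and SAP 2.7 is silent on it. Lack of adjustment does not cause this, and apart from Fisher (about 1.5 points less power) it hardly matters numerically.

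**What to change.** Dated before final unblinding, and carried into protocol 8.4 and SAP 2.7 as well as SAP 4.3.1:

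1. Name one primary test on the FAS: logistic regression with treatment, the onset stratum as randomised, baseline NIHSS and age, with site as a random intercept or pooled, not as some 40 fixed dummies. Check the type I error of the chosen site handling by simulation, since the gains in step 4 were computed for onset, NIHSS and age only.
2. Report the risk difference standardised from that model, with its confidence interval, to match the estimand. Keep the unadjusted comparison as supportive.
3. Use the same covariates for the binary secondaries, and state a baseline NIHSS term for the Day 14 change.
4. State that the interim Z came from the unadjusted model and that no change in sample size followed.

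The third IDMC minutes (25 December 2022) record agreement to lock the database. If the data are already unblinded, leave the unadjusted analysis as primary and label the adjusted one supportive.

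The cost is SAP wording, a matching protocol amendment and a few lines of code. The small downside is that the adjusted odds ratio is conditional and will differ from the marginal one. Both equal 1 when treatment has no effect, so the success rule keeps its meaning.

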**5) Data derivation and transformation:**

- Age: Year is used as unit, = (date of informed consent – date of birth)/365.25, rounded.
- Time from treatment to onset = time of first dose – time of stroke onset in hours (h) rounded to one decimal place.
- Stroke onset time is defined as the time at which the patient 's symptoms begin, and if it starts during sleep, the time at which the last manifestation is normal should be used as the time of onset. If stroke onset time is completely missing, impute with 0h0m on day of onset; if only minutes are missing, impute with 0m.
- Estimated glomerular filtration rate (eGFR):
- $eGFR (ml/min/1.73m^2) = 186 * (Scr/88.4)^{-1.154} * (age)^{-0.203} * 0.742$  (if female) \* 1.233

Where Scr is serum creatinine (umol/L), age is age, and female is female.

Renal function: normal renal function (baseline eGFR  $\geq$  90), mild renal impairment ( $60 \leq$  baseline eGFR < 90), and moderate to severe renal impairment (baseline e GFR < 60).

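### Sensitivity Analysis 5 and the onset subgroup use onset-to-first-dose time, not the onset stratum used at randomisation, with no rule for undosed patients and an unspecified site term

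*Combined protocol and SAP*

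**What the plan says.** SAP section 2.6 introduces the design factors with "Randomization will be stratified by" and lists onset time, cut at 24 hours, and investigational site. Protocol section 5.3 gives the same two factors.

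In SAP section 4.3.1, Sensitivity Analysis 5 is a logistic regression on treatment, "baseline time from actual treatment to onset" (cut at 24 hours) "and study site as covariates". The subgroup list in the same section has "Actual treatment to Onset Category 1" with the same cut.

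SAP section 4.1.3 gives the derivation: "Time from treatment to onset = time of first dose" minus the time of stroke onset. When the onset clock time is wholly missing, the instruction is "impute with 0h0m on day of onset"; when only the minutes are missing, they are set to zero.

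Four other provisions matter:
- Protocol section 5.5 places the first dose after randomisation.
- SAP section 3 puts every randomised subject in the FAS, and section 4.3.1 runs the sensitivity analyses on the FAS alone.
- SAP section 4.1.2 imputes nothing except the primary efficacy measure.
- The fallback in SAP section 4.1.3 for a missing first-dose date covers only subjects who took trial medication.

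The primary logistic regression in SAP section 4.3.1 names no covariates.

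**The concern.** The primary model is unadjusted, so Sensitivity Analysis 5 is the one pre-specified efficacy analysis of the primary endpoint that brings in factors of the kind used to stratify. A reader will look to it for reassurance that ignoring the strata did no harm. It should therefore use the strata as randomised and keep all randomised patients.

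On the onset factor it does neither with certainty. The variable is called baseline but depends on something that happens after allocation, and it does not exist for a patient who was randomised and never dosed. The rule for a missing clock time pushes in one direction only. Site is a genuine design factor, but the SAP does not say whether it is a fixed effect, a random effect or a conditioning stratum, and gives no rule for pooling small sites. At stake is a supportive odds ratio and one subgroup contrast, not the primary result.

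**Working it through.** **1. The plan's own figure.** Inputs from SAP section 2.5: 50% against 40%, two-sided alpha 0.05, "a power of 80%, and a randomization ratio of 1:1". With pooled variance and no continuity correction:

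n = [1.960 × √(2 × 0.45 × 0.55) + 0.842 × √(0.25 + 0.24)]² / 0.10² = (1.379 + 0.589)² / 0.01 ≈ 387.3, so 388 per arm. Then 388 / 0.85 = 456.5, so 457 per arm and 914 in all. The plan's figures reproduce. The implied odds ratio is (0.5/0.5) / (0.4/0.6) = 1.50, log 0.405, with standard error √[1/(457 × 0.25) + 1/(457 × 0.24)] ≈ 0.134.

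**2. Which onset variable.** The randomisation stratum must be known when the allocation is requested. Onset-to-first-dose time is known only once the dose is given. The two differ for any patient who passes 24 hours between randomisation and first dose, or whose onset time is later revised or imputed.

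**3. Undosed patients.** The documents do not say how many there were. Each 1% is 0.01 × 914 ≈ 9 patients. The simulation had 600 trials per scenario, 914 patients, 39 uneven sites, site SD 0.5 on the logit scale and true odds ratio 1.50. Undosed patients were equally likely in both arms and had no treatment effect (30% or 0% response). The model had site and onset effects.

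| Undosed (assumed) | OR, all kept | OR, undosed dropped | Rise |
|---|---|---|---|
| 1% | 1.517 / 1.533 | 1.525 / 1.539 | about 0.5% |
| 3% | 1.503 / 1.502 | 1.524 / 1.520 | about 1.3% |
| 5% | 1.502 / 1.504 | 1.538 / 1.536 | about 2.3% |

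The paired values are for 30% and 0% response in undosed patients.

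**4. Missing clock time.** Setting onset to the start of its day can only lengthen the interval, by up to 24 hours. As an illustration, onset at 18:00 and first dose at 02:00 the next day is truly 8 hours; with the clock time lost it becomes 26 hours, and the patient moves to the later category. No move in the other direction is possible.

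**5. Site as fixed effects (one reading of the SAP).** The third IDMC minutes give 914 patients from 39 sites, so 914 / 39 ≈ 23 per site. A rough inflation factor for the log odds ratio under unconditional maximum likelihood is N/(N − K) = 914/875 = 1.045, so 0.405 × 1.045 ≈ 0.423, or OR 1.53. Simulation used 600 trials per row (1,500 at the null), with blocks of four within site by onset (block size assumed):

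| Sites | Site SD | True OR | Unadjusted | Site dummies + onset | Mantel-Haenszel, site × onset |
|---|---|---|---|---|---|
| equal | 0 | 1.50 | 1.497 | 1.525 | 1.496 |
| equal | 0.5 | 1.50 | 1.459 | 1.518 | 1.491 |
| uneven | 0 | 1.50 | 1.494 | 1.520 | 1.495 |
| uneven | 0.5 | 1.50 | 1.475 | 1.534 | 1.508 |
| uneven | 0.5 | 1.00 | 1.003 | 1.003 | 1.003 |

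Dummies against Mantel-Haenszel differ by 0.017 to 0.019 on the log scale, which is 0.017/0.134 to 0.019/0.134, or 0.12 to 0.14 standard errors. At the null, rejection was 5.5% against 4.3% unadjusted (Monte Carlo error about 0.6 points).

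A separate simulation (39 equal sites, site SD 0.3) checked direction. At a true OR of 1.5 the log OR was 0.426 with dummies and 0.408 with Mantel-Haenszel; at 0.67 it was −0.428 and −0.410; at 1.0 both were 0.010. The standard error also grew (0.138 against 0.135), so at 1.5 the mean z moved only from 3.01 to 3.07.

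**The case against.** Actual onset-to-dose time is a defensible choice. Protocol section 4.3 measures the 48-hour window to first administration, so this is the trial's own clinical time scale. Blinding makes a difference between arms in dosing delay unlikely. Dosing is meant to follow randomisation promptly, so few patients should cross 24 hours and few should go undosed. A patient with no onset clock time also needed some convention at randomisation, and the documents give none. All of this stands as a limit on size. It does not supply a value for an undosed FAS patient, and it does not make the variable the design stratum.

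Three stronger readings are tempting and are not supported:
- **That adjusting for site departs from the design.** Site is a stratification factor; only the onset variable departs.
- **That the adjusted model favours the drug by construction.** Fixed site effects are only one reading of the SAP. Even so, the stretch is the same for benefit and harm and vanishes at OR 1.00. Part of any gap from the unadjusted OR (1.46 to 1.48 when sites differ) is non-collapsibility, not bias.
- **That undosed patients are dropped.** The SAP states no deletion rule. Omission is what default software would do.

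Nor are sites with all or no responders an argument for changing the method. With uneven sites they hold some 5 to 8 patients, and they contribute nothing to conditional logistic regression or Mantel-Haenszel either.

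**Conclusion.** The point holds as a minor one. Sensitivity Analysis 5 and the onset subgroup use a variable fixed after randomisation in place of the recorded onset stratum. They leave undosed FAS patients without a rule, and the missing-time rule can only move patients towards the later category.

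The effects are small. Omitting undosed patients adds about 0.5% to 2.3% to the odds ratio if 1% to 5% were undosed without benefit; that share is assumed. Fixed site effects, if that is what is meant, turn 1.50 into about 1.52 to 1.53, with no shift at 1.00. The number of patients reclassified around 24 hours, or with a missing clock time, cannot be worked out from the documents. The primary analysis names no covariates and is untouched.

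**What to change.** In Sensitivity Analysis 5 and the onset subgroup, use the onset stratum recorded by the randomisation system. It exists for every FAS patient, so no rule for undosed patients is then needed in the covariate. Keep actual onset-to-dose time as a supplementary variable, with the number of patients lacking it reported.

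Specify the site term: conditional logistic regression with site as the stratum and the onset stratum as a covariate, or Mantel-Haenszel over site × onset. Do not fit the 78 site-by-onset cells as fixed effects: 914/836 = 1.093 would take the rough figure for a true 1.50 to about 1.56.

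The cost is one line of SAP text and a change of model statement. If the drug works, the supportive odds ratio becomes slightly less favourable. The third IDMC minutes record complete follow-up and agreement to lock the database, so if the SAP can no longer be amended, the result can be reported as a labelled supplementary analysis with no new data.
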